### Interventions

In the nutritional intervention, men are randomised to either a lycopene supplement intervention or a plant-based intervention or a nutritional control arm. The lycopene intervention involves one 10 mg lycopene capsule daily (provided to the man). The plant-based intervention comprises eating as many portions of fruit and vegetables daily as possible, aiming for at least five portions, and swapping dairy milk for non-dairy alternatives, for example, soya milk, as often as the men can. The control arm men carry on with their usual diet; if the men ask for nutritional advice, standard, publically available, information is provided.

In the physical activity intervention, men are randomised to either walking at a brisk pace for 30 minutes, on at least five days a week, on top of their usual physical activity or to continue with their usual levels of physical activity.

The men are provided with materials and detailed instructions specific to their allocated intervention arm by trained research nurses and asked to follow their allocated intervention arm for 6 months.

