## Methods/design

### Trial setting and participants

The PrEvENT trial has a 2 x 3 factorial design (resulting in six different experimental conditions), where men are randomised to levels of both a physical activity and nutritional intervention. Randomisation is carried out by the Bristol Randomised Trial Collaboration [30] using a web based system. Participants and the research team are not blinded; only the trial statistician will be blinded. The trial is being conducted under the auspices of the National Institute for Health Research (NIHR) Bristol Biomedical Research Unit in Nutrition, Diet and Lifestyle [31]. The feasibility trial is being conducted at the North Bristol National Health Service (NHS) Trust. Inclusion and exclusion criteria are listed in Table 1.

**Table 1 Tab1:** PrEvENT inclusion and exclusion criteria

Inclusion criteria
• Clinically localised prostate cancer
• Listed for radical prostatectomy
• Capacity to provide informed consent
• Aged 18 or over
• Sufficient understanding of the English language
Exclusion criteria
• Unable to provide informed consent
• Unsuitable to participate following guidance from their clinician
• Unable to undergo follow-up
• Factors that constrain participation in any aspect of the intervention, including:
o Co-morbidities, for example:
▪ Congestive heart failure or angina, recent myocardial infarction or breathing difficulties requiring oxygen use or hospitalisation
o Unable to walk without the aid of a mobility aid (other than a walking stick)
o Religious beliefs
o Allergy to lycopene
• Current heavy consumers of the nutritional element of the intervention, that is, taking daily lycopene supplements for more than 3 months
• Current participation in high levels of regular physical activity, for example doing strenuous activity five or more times a week for long enough to work up a sweat
• Any additional reason for not being able to participate in any aspect of the intervention

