### Primary outcome measures

Co-primary outcomes are randomisation rates (the proportion of eligible men who agree to be randomised) where a rate of 65 % or above would be considered acceptable [33] and adherence to the interventions at 6 months following randomisation, where a rate of 75 % or above would be considered acceptable. Adherence will be calculated for both the nutrition and physical activity interventions and is taken to be following intervention instructions > 90 % of the time. Adherence to the nutrition intervention will be assessed by participant self-report on the daily monitoring form. This form is completed daily by the participants for the duration of the 6-month intervention. For the lycopene arm, men are asked if they took their supplement daily - yes/no; for vegetable and fruit consumption, men are asked how many portions they consumed daily; for dairy milk consumption, men are asked how much of their dairy milk they replaced with an alternative – all/some/none. Adherence to the physical activity intervention will be assessed by their self-reported adherence to the recommended minimum 30 minutes of brisk walking five times per week during the 6-month intervention phase.

In order to assess the adherence rate with a confidence interval of ± 5 % and an estimated expected adherence rate of 75 %, the required minimum sample size for this feasibility study would be approximately 75 participants [34]. Incorporating an expected randomisation rate of 80 %, we intend to recruit at least 100 men into this study.

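### Walking is prescribed as additional activity but adherence is scored against an absolute target, so the co-primary adherence rate can mix uptake with existing habit

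*Protocol article*

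**What the plan says.** **Walking instruction.** The Interventions section asks for half an hour of brisk walking "on at least five days a week, on top of their usual physical activity".

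**Adherence.** Primary outcome measures defines adherence in general as "following intervention instructions > 90 % of the time" and sets the bar for this co-primary outcome, "where a rate of 75 % or above would be considered acceptable". For walking, it then says that adherence will be assessed by "self-reported adherence to the recommended minimum 30 minutes of brisk walking five times per week".

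**Plant-based arm.** The instruction is "eating as many portions of fruit and vegetables daily as possible, aiming for at least five portions", together with swapping dairy milk for alternatives. For fruit and vegetables, "men are asked how many portions they consumed daily". For milk, the form records whether all, some or none was replaced.

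**Eligibility (Table 1).** The nutritional exclusion reads "Current heavy consumers of the nutritional element of the intervention, that is, taking daily lycopene supplements for more than 3 months". The activity exclusion covers high regular activity, and its example is "doing strenuous activity five or more times a week for long enough to work up a sweat".

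**Background.** The Physical activity section describes brisk walking as moderate intensity. It says that most men with prostate cancer fall short of the activity guideline, but gives no figure.

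**The concern.** The walking intervention is an increment over what a man already does, whereas the stated assessment is a fixed weekly amount. The two agree for a man who starts from no brisk walking. They part for a man who already walks the target amount: under the assessment sentence he can be scored adherent from the first week, although he has added nothing.

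The portion count raises a similar problem. A man who already eats five portions meets the minimum aim without changing his diet.

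Adherence is one of two co-primary outcomes, is judged against a fixed 75%, and is meant to inform a larger trial. If some men reach the target by habit, the observed rate is partly a measure of who enrolled. The bar could then be passed with lower uptake among the men who had something to change.

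**Working it through.** **1. Can men already at target enter, and be scored adherent unchanged?**

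| Component | Instruction | Assessment | Excluded if already doing it? | Can be met unchanged? |
|---|---|---|---|---|
| Walking | Additional to usual activity | Fixed weekly amount, self-reported | Not clearly: the example is strenuous activity, and brisk walking is called moderate | Yes, by the assessment sentence |
| Fruit and vegetables | As many as possible, aiming for at least five | Daily count of portions | No criterion | Yes, for this component |
| Dairy milk | Swap as often as possible | All, some or none replaced | No criterion | Not by a man who still drinks dairy milk: he would answer none |
| Lycopene | Take the supplied capsule | Taken daily, yes or no | Yes, daily supplement users of more than 3 months | No |

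The article gives no rule for combining the two plant-based components into one adherence status. Meeting the portion component alone is therefore not the same as being adherent in that arm.

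**2. How far could this move the rate?** The article has no figure to reproduce, so this is an illustration. Let:
- b = share of an arm already at target (assumed);
- c = adherence among those men;
- a = adherence among the others.

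Observed adherence = b × c + (1 − b) × a.

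With c = 1 (every man at target stays adherent for six months), setting the observed rate to 0.75 gives a = (0.75 − b)/(1 − b):

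| b (assumed) | Calculation | Adherence needed among the others | Observed rate if a = 60% (assumed) |
|---|---|---|---|
| 0% | 0.75/1.00 | 75.0% | 60% |
| 10% | 0.65/0.90 | 72.2% | 64% |
| 20% | 0.55/0.80 | 68.8% | 68% |
| 30% | 0.45/0.70 | 64.3% | 72% |
| 40% | 0.35/0.60 | 58.3% | 76% |

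If the others adhere at 60%, the bar is reached only when b = (0.75 − 0.60)/(1 − 0.60) = 37.5%.

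**3. Why these are upper bounds.** For a given b, c = 1 gives the lowest a. If men at target also adhered at 75%, then a = 75% whatever b is, and there is no distortion.

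**4. Precision of a split by baseline status.** Assume 80 men randomised, equal allocation, and 30% at target.
- Walking: 40 × 0.70 = 28 men below target.
- Plant-based: 80/3 × 0.70 ≈ 19 men below target.
- At 64% adherence, the 95% half-width is 1.96 × √(0.64 × 0.36/n), about 18 points for 28 men and 22 points for 19.

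**The case against.** The strongest reply is that the governing definition is following the intervention instructions, and those instructions include walking beyond usual activity. On that reading, a man who adds nothing is not adherent, and the later sentence only describes data collection. This is a fair reading and it limits the point: the article does not firmly fix a rule that counts such men. It leaves two sentences that give different answers for the same man, which still need reconciling.

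Three stronger readings might be inferred, and the article does not support them:
- **That men who change nothing are in general scored adherent.** This can apply only to men already at target, who are a minority for activity. In the plant-based arm, a five-portion eater who keeps drinking dairy milk meets one of two components. The lycopene arm is unaffected.
- **That only strenuous exercisers are excluded.** Strenuous activity is given as an example of high activity, not as its limit. Whether habitual brisk walkers are screened out is unclear.
- **That the rate in men below target is the one to carry forward.** Compliance with instructions is a legitimate feasibility measure. If the larger trial keeps the same eligibility, the overall rate is the one that transfers.

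It can also be said that change is already analysed. The Analysis plan does include change in activity and in fruit and vegetable intake, and diet and activity are measured at both baselines. Those analyses are exploratory, however, and do not enter the co-primary adherence rate.

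**Conclusion.** The point holds as an inconsistency with a cheap remedy. For walking, the instruction is incremental and the stated assessment is absolute, and eligibility does not clearly remove men for whom the difference matters. For the plant-based arm, only the portion component is exposed. The co-primary adherence rate can therefore combine uptake with existing habit.

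The size is unknown because the article gives no share of men already at target, for activity or for diet. At assumed shares of 10% to 40%, the adherence needed among the other men falls from 75% to between 72% and 58%. This rests on every man at target staying adherent, so it bounds the effect and does not estimate it. For the plant-based arm, the illustration applies only to men who already meet whatever combined rule is adopted.

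**What to change.** 1. Reconcile Interventions with Primary outcome measures: state whether walking adherence is scored against the absolute weekly amount or as an addition to usual activity. State also how the portion and dairy components combine into plant-based adherence.
2. Keep the overall adherence rate as the co-primary figure, judged against 75%.
3. Beside it, for the walking and plant-based arms, report adherence with 95% confidence intervals in men below target and in men at target at baseline. Write down beforehand how the questionnaire answers and accelerometry define being at target.
4. Classify walking by the pre-surgery cohort baseline as well as the true trial baseline. The latter follows a questionnaire posted five weeks after surgery, when activity may be unrepresentative.

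Table 2 shows the food frequency questionnaire, the physical activity questionnaire and accelerometry at both baselines, so no new data are needed. The cost is wording, two extra rows of results, and small subsets with half-widths of roughly 18 to 22 points under the assumptions above. The split should therefore be read as descriptive.

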### Primary outcome measures

Co-primary outcomes are randomisation rates (the proportion of eligible men who agree to be randomised) where a rate of 65 % or above would be considered acceptable [33] and adherence to the interventions at 6 months following randomisation, where a rate of 75 % or above would be considered acceptable. Adherence will be calculated for both the nutrition and physical activity interventions and is taken to be following intervention instructions > 90 % of the time. Adherence to the nutrition intervention will be assessed by participant self-report on the daily monitoring form. This form is completed daily by the participants for the duration of the 6-month intervention. For the lycopene arm, men are asked if they took their supplement daily - yes/no; for vegetable and fruit consumption, men are asked how many portions they consumed daily; for dairy milk consumption, men are asked how much of their dairy milk they replaced with an alternative – all/some/none. Adherence to the physical activity intervention will be assessed by their self-reported adherence to the recommended minimum 30 minutes of brisk walking five times per week during the 6-month intervention phase.

In order to assess the adherence rate with a confidence interval of ± 5 % and an estimated expected adherence rate of 75 %, the required minimum sample size for this feasibility study would be approximately 75 participants [34]. Incorporating an expected randomisation rate of 80 %, we intend to recruit at least 100 men into this study.

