### Analysis plan

The primary comparative analyses will be by intention-to-treat. Baseline characteristics of each group will be tabulated using means and standard deviations for normally distributed data, medians and interquartile ranges for non-normally distributed data, and percentages and counts for categorical data. Randomisation rate and adherence to the intervention will both be reported as a percentage, along with the respective 95 % confidence interval.

We will also conduct exploratory analyses of change in physical activity and fruit and vegetable consumption (as measured for adherence to the interventions) will be analysed using a two-way ANOVAs or appropriate non-parametric tests if necessary. Change in selected secondary outcomes (IGF-I, PSA and blood biomarkers) will be analysed similarly, although this study is not powered for secondary outcomes. These analyses will focus on the main effects of the interventions, but we will also explore possible interactions between the interventions with respect to these outcomes. Assuming 80 men are recruited into the trial, this will provide approximately 90 % power to detect a large main effect size (f = 0.4) with an alpha level of 0.05, analysing the study as a 2 x 3 factorial design (power will be reduced after correcting for multiple testing). We will also explore associations between baseline Stage of Change; behavioural, normative and control beliefs; and adherence to the interventions using chi-square tests and logistic regression models.

Qualitative data collected during this research will be analysed thematically using a qualitative method, such as the framework approach [38]. Individuals will not be identified by name in the written transcript. A qualitative analysis computer programme, such as NVivo [39], will be used to assist analysis.

The SPIRIT 2013 checklist [40] and the CONSORT statement [41] were followed and adhered to during the development of the trial protocol and implementation. The PrEvENT trial has been given full ethical approval by Cornwall and Plymouth Research Ethics Committee (REC), ref: 14/SW/0056, and registered on the ISRCTN registry, ref number ISRCTN99048944. All participants provide fully informed consent.

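### The sample size treats all 75 men as informing one adherence rate, but the two adherence rates rest on about 40 men (walking) and 53 men (nutrition)

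*Protocol article*

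**What the plan says.** All of the following is in the protocol article.

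- **Primary outcome measures** makes adherence at 6 months a co-primary outcome, with 75% or above taken as acceptable. It says: "Adherence will be calculated for both the nutrition and physical activity interventions". The measures listed are taking the capsule (lycopene arm), portions of fruit and vegetables, replacement of dairy milk, and brisk walking for 30 minutes five times a week. No adherence measure is given for control men.
- **Interventions** describes the nutrition factor: "men are randomised to either a lycopene supplement intervention or a plant-based intervention or a nutritional control arm". For the physical activity factor, the alternative to brisk walking is "or to continue with their usual levels of physical activity". Nutrition controls keep to their usual diet.
- **The sample size**, also in Primary outcome measures, is set for one rate: "In order to assess the adherence rate with a confidence interval of ± 5"%, with "an estimated expected adherence rate of 75"%, leads to "the required minimum sample size for this feasibility study would be approximately 75 participants". The only inflation is for randomisation: "Incorporating an expected randomisation rate of 80 %, we intend to recruit at least 100 men into this study".
- **Recruitment into the randomised control trial** plans at least 80 randomised out of a cohort of 100.
- **Analysis plan** says that randomisation rate and adherence "will both be reported as a percentage, along with the respective 95 % confidence interval".

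**The concern.** The sizing treats adherence as one proportion observed in every randomised man. The outcome definition gives at least two proportions, each defined by actions that only some men are asked to take. In a 2 x 3 factorial with equal allocation, half the men have no walking programme and a third have no nutritional change to make. Nothing in the calculation allows for them.

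Precision on adherence is the justification given for the number of men, and the 75% threshold is meant to inform a larger trial. If the denominators are smaller than the calculation assumes, each comparison with 75% is less certain than the article implies, and an intervention with inadequate adherence is more likely to appear acceptable.

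**Working it through.** **Inputs.** Expected adherence p = 0.75, half-width 0.05 and n of about 75 come from Primary outcome measures. The 95% level comes from Analysis plan; the sample-size sentence gives no level. At least 80 randomised comes from the RCT recruitment section, and the 2 x 3 design from Trial setting and participants. Equal allocation is assumed because the article states no ratio.

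**1. Reproducing the 75.** For a single proportion, n = z² p(1 − p) / d².

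- 95% confidence, ±5 points: 1.96² × 0.1875 / 0.0025 = 288.1, so 289 men.
- z = 1 (±5 as one standard error): 0.1875 / 0.0025 = 75 exactly.
- 95%, ±5, with a finite-population correction to 100 men: 288.1 / (1 + 287.1/100) = 74.4.
- 95%, ±10 points: 1.96² × 0.1875 / 0.01 = 72.0, so 73 men.

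The article states none of the last three readings. At 95% confidence, 75 men give 1.96 × √(0.1875/75) = ±9.8 points. That shortfall from ±5 exists before any question of denominators and must be kept apart from it.

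**2. Denominators.** With 80 randomised:

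- walking: 80 × 1/2 = 40
- either active nutrition arm: 80 × 2/3 = 53.3
- lycopene alone, or plant-based alone: 80 × 1/3 = 26.7

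With only the stated minimum of 75 randomised, these become 37.5, 50 and 25.

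**3. Precision at 75% adherence.** One standard error is √(0.1875/n); the 95% half-width is 1.96 times that.

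| Men in the rate | One standard error | 95% half-width |
|---|---|---|
| 75 (all men, as sized) | 5.0 | 9.8 |
| 53 (nutrition) | 5.9 | 11.7 |
| 40 (walking) | 6.8 | 13.4 |
| 27 (one nutrition arm) | 8.3 | 16.3 |

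The loss due to the denominator, like for like, is therefore ±9.8 to ±11.7 or ±13.4 at 95%. On the one-standard-error reading that reproduces 75, it is ±5.0 to ±5.9 or ±6.8.

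**4. Effect on the 75% threshold.** Suppose true adherence is 65%. The binomial chance of observing at least 75% is:

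- n = 40, 30 or more adherent: 12.1%
- n = 53, 40 or more adherent: 7.0%
- n = 75, 57 or more adherent: 2.8%

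**5. Exact 95% intervals near 75%.** 30/40 gives 58.8% to 87.3%; 40/53 gives 61.7% to 86.2%; 20/27 gives 53.7% to 88.9%.

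**The case against.** **Most of the distance from ±5 is a different error.** This stands. With every man counted, 75 still gives only ±9.8 at 95%. Setting ±13.4 against ±5 would charge the whole gap to the denominator, so ±9.8 is the proper benchmark. Correcting the confidence level alone would still leave the denominators wrong.

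**The article names two rates, not three.** A reader might infer a separate co-primary rate for each nutrition arm, with about 27 men each. The text refers to the nutrition intervention in the singular, so the supported denominators are about 40 and 53. The arm-specific data items make reporting by arm reasonable, and the figure of 27 applies only then.

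**Controls might be counted as adherent.** A reader might infer that the rates will be inflated in this way. If all controls were pooled and scored adherent, true walking adherence of 50% would show as 0.5 × 0.50 + 0.5 = 75%, and true nutrition adherence of 62.5% as 2/3 × 0.625 + 1/3 = 75%. The article plans neither step and defines no adherence measure for controls. This is a reason to state the exclusion, not a fault in the plan. Pooling men with any active component would give 80 × 5/6, about 67 men, which is still under 75 and is not the separate calculation described.

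**The chance of reaching 75% when true adherence is exactly 75% might look like evidence.** It is 58% at n = 40, but it is near one half at any size (48% at n = 75), so it shows nothing about the denominators.

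**This is a feasibility trial.** No formal stop/go test is attached to the 75%, and 95% intervals will be reported, so rates computed on allocated men would show their own uncertainty. That limits the harm. It does not make the sample-size statement correct. How men without returned forms are counted is commonly left to the SAP and is not part of this point.

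**Conclusion.** The point holds. The article's precision statement counts men who have no intervention to adhere to, and so conflicts with its own definition of the outcome. The rates will rest on about 40 and 53 men, with 95% half-widths of about ±13.4 and ±11.7 points where 75 men would give ±9.8. The risk of a true 65% passing as 75% or more rises from about 3% to about 12% (walking) or 7% (nutrition).

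These figures assume equal allocation, 80 men randomised, complete adherence data and a true rate of 75% for the half-widths. Fewer men or missing forms would widen the intervals further. The ±5% is also unattainable at 95% confidence with all 75 men, and the two errors should be corrected together. The documents do not support saying that the plan will inflate adherence, or that the whole shortfall from ±5 comes from the denominators.

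**What to change.** 1. State that each adherence rate is estimated among the men randomised to that active intervention, with controls excluded, since scoring them as adherent would raise the rate.
2. Replace the ±5% on 75 men with the 95% precision attainable: about ±13.4 points for walking (about 40 men) and ±11.7 for nutrition (about 53). If the nutrition arms are reported separately, give about ±16.3 for each (about 27). State the confidence level and the allocation ratio used.
3. Read each 75% threshold together with that rate's own 95% interval.

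The cost is a change of wording and a less favourable stated precision. No extra patients or data are needed. Keeping ±5% at 95% confidence instead would take 289 men per rate, or about 578 randomised for walking (289 × 2) and 434 for nutrition (289 × 1.5), which is far beyond the planned size of this trial.

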### Recruitment into the randomised control trial

Men invited to participate in the RCT will have agreed to be contacted about further related research during the initial cohort recruitment phase. Along with the post-surgery follow-up data collection questionnaire, these men receive an invitation to participate in the RCT. They are telephoned by the research nurse and screened for trial eligibility. Inclusion and exclusion criteria for the RCT can be seen in Table 1. Where eligible, a research appointment is arranged for the following week, where a consent form is completed along with collection of blood samples and provision of an accelerometer (to capture intensity of physical activity) to wear continuously for the following week. All men are also provided with a pedometer (to measure daily step count), to wear for the 6-month duration of the trial. The data items that are being collected are listed in Table 2.

The men are randomised into both the nutritional and physical activity intervention arms of the trial and provided with instructions specific to their intervention allocation. They receive texts, emails and post relating to the trial interventions, including recipe ideas and motivational messages, as applicable to their allocated intervention, to encourage continuation of their trial arm intervention throughout the 6-month trial period. These contacts take place at 1, 2, 5, 8, 13, 15 and 18 weeks post-randomisation. They include gratitude for ongoing support of the research and a reminder of the importance of the data collected. Men are reminded of the changes they have been asked to make and the data they have been requested to record daily. Instructions are given of how to carry out the behaviour change, as well as being reminded of the potential benefits of the new behaviour, and men are informed that others similar to them carry out the intended behaviour. Message content was developed in line with the Theory of Planned Behaviour [32] (See Theoretical Underpinning below).

At 3 and 6 months following randomisation, the men attend a follow-up research appointment, where repeat questionnaires are completed. At the 6-month follow-up appointment, a blood sample is taken. For the final week of the trial, men wear an accelerometer to record the intensity of their physical activity.

We intend to recruit 100 men to the cohort, and of these, randomise at least 80 to the randomised controlled trial.

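### About 75 men do not estimate a 75% adherence rate to within ±5 points: the 95% interval is about ±10 points, and wider if only men in active arms count

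*Protocol article*

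**What the plan says.** Under Primary outcome measures, adherence at 6 months is one of two co-primary outcomes, and a rate of 75% or more counts as acceptable. The sample size follows from a precision target. The aim is to "assess the adherence rate with a confidence interval of ± 5" per cent, with "an estimated expected adherence rate of 75" per cent, from which "the required minimum sample size for this feasibility study would be approximately 75 participants". A reference is cited, but neither a formula nor a confidence level is given. The next step is "Incorporating an expected randomisation rate of 80 %, we intend to recruit at least 100 men into this study".

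Two other sections bear on this:

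- Analysis plan fixes the level of the interval: "Randomisation rate and adherence to the intervention will both be reported as a percentage, along with the respective 95 % confidence interval".
- Recruitment into the randomised control trial gives the planned numbers: "We intend to recruit 100 men to the cohort, and of these, randomise at least 80 to the randomised controlled trial".

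Primary outcome measures also says that adherence is calculated for the nutrition and the physical activity interventions. Under Interventions, each of these two factors has a control level at which men carry on as usual.

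**The concern.** The target precision, the expected rate and the resulting number of men do not agree at the confidence level that the article uses for reporting. A proportion near 75% estimated from 75 people has a standard error of 5 percentage points, so a 95% interval should be roughly twice as wide as stated.

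This is the only calculation in the article that derives the sample size for a primary outcome. A reader would expect an observed 75% to come with an interval of about 70% to 80%. The interval actually reported would run from the mid-60s to the mid-80s. That matters because adherence is compared with a 75% threshold and the results are meant to inform a larger trial.

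**Working it through.** **Inputs.** Expected adherence p = 0.75, half-width d = 0.05 and n of about 75 (Primary outcome measures). Level 95%, two-sided, z = 1.96 (Analysis plan, because the sample-size sentence gives no level). Planned number randomised, at least 80 (Recruitment into the randomised control trial).

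**Formulas.** n = z² p(1 − p)/d², and half-width = z √(p(1 − p)/n), with p(1 − p) = 0.1875.

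**Attempt to reproduce 75.** With d = 0.05:

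| Reading | z | n required |
|---|---|---|
| 95% two-sided | 1.960 | 288.1, so 289 |
| 90% two-sided (or 95% one-sided) | 1.645 | 202.9, so 203 |
| 80% two-sided | 1.282 | 123.2, so 124 |
| One standard error | 1 | 75.0 |

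Reading 5% as the total width (d = 0.025) gives 1,153 at 95%. Other interval methods at 95% give similar answers to the first row: 286 (Wilson) and about 306 (Clopper-Pearson). Of the readings in the table, only z = 1 returns 75, and ±1 standard error is a 68.3% interval.

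**Precision that the planned numbers give at 95%.**

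- n = 75: standard error √(0.1875/75) = 0.0500; half-width 1.96 × 0.0500 = 0.098, or ±9.8 points (65.2% to 84.8%).
- n = 80: 1.96 × √(0.1875/80) = 0.095, or ±9.5 points.
- A half-width of 10 points needs 1.96² × 0.1875/0.01 = 72.0 men, close to the stated 75.
- An observed 56 of 75 (74.7%) has a Wilson 95% interval of 63.8% to 83.1% and a Clopper-Pearson interval of 63.3% to 84.0%.

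**Denominator.** The figures above need all 75 men to contribute. The article does not state the allocation ratio. Assume equal allocation of 75 men, and adherence assessed only in men given something to change:

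| Group | n | 95% half-width |
|---|---|---|
| Walking | 37.5 | 1.96 × √(0.1875/37.5) = ±13.9 points |
| Two nutrition arms combined | 50 | 1.96 × √(0.1875/50) = ±12.0 points |
| One nutrition arm | 25 | 1.96 × √(0.1875/25) = ±17.0 points |

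**Recruitment step.** 75/0.80 = 93.75, or 94 men, so the target of 100 is consistent with 75. The discrepancy lies only in the step from ±5% to 75.

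**The case against.** The sample-size sentence gives no confidence level and rests on a reference that is not at hand, so the authors may have had a route that the article does not show. One such route exists. The 95% formula with a finite-population correction for N = 100 gives 288.1/(1 + 287.1/100) = 74.4, which could be called approximately 75. A reader who sees that z = 1 gives exactly 75.0 might infer that the multiplier 1.96 was left out. The documents do not establish this: no formula is printed and two routes arrive near 75. What stands is that the cause is unknown. The correction would not rescue the claim, however. It is not mentioned, the article derives the 100 from the 75 and not the reverse, and the results are meant to inform a larger trial in other men.

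A second objection is that this is not the only statement about size. The Analysis plan section gives about 90% power for a large main effect (f = 0.4) with 80 men. That is true, but the statement belongs to exploratory analyses and does not support the precision of a primary outcome.

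Third, little changes in practice. The acceptability rule is worded as a rate of 75% or above, with no reference to the interval limits. This is a feasibility trial, recruitment was well advanced (69 men), and the actual 95% interval will be reported. All of this stands. It limits the consequence to a misstated design expectation, but it does not make the printed figure correct.

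**Conclusion.** The stated precision is wrong as written. At the 95% level to which the article commits, 75 men at 75% adherence give about ±9.8 points (±9.5 with 80), not ±5, and ±5 points would need about 289 men. None of the conventional levels tried (80%, 90%, 95%) gives 75. The figure is consistent with taking one standard error as the half-width, and no more than that can be said about its origin.

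The ±10 points assumes that every man contributes to the adherence rate. If only men in active arms count, the half-width is about 12 to 17 points, depending on the group and assuming equal allocation.

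A reader might go further and infer that the trial is too small and should be enlarged to 289, or that the acceptability rule fails. The documents do not support either reading. They set no requirement that depends on ±5 points beyond this sentence, and the threshold applies to the observed rate.

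**What to change.** Keep the sample size and replace the precision statement with one that gives the level and the denominator. For example: *If all 75 men contribute and adherence is 75%, the 95% confidence interval is about ±10 percentage points. If adherence is assessed only in men allocated to an active intervention (assuming equal allocation), it is about ±14 points for walking (n about 37), ±12 for the two nutrition arms combined (n = 50) and ±17 for one nutrition arm (n = 25).* Keep only the part that matches the denominator actually used, and adjust the numbers if the allocation ratio differs.

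Interpret the 75% acceptability threshold with the same precision in view.

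The cost is a short change of text and a less favourable stated precision. No extra participants are needed, and neither conduct nor analysis changes.
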